#### Stimuli

Stimuli will consist of individualized treatment targets that will be included in treatment sessions and a generalization corpus containing a common set of words that all children will produce. Treatment targets will consist of 20 words or phrases that may be targeted over the course of treatment. They will be selected by evaluating each child’s performance across assessment tasks, including their phonetic inventory, word shape inventory, lexical stress patterns, individual error profile with a specific focus on vowel errors, and responses to clinician cueing within dynamic assessment tasks (e.g., *DEMSS*). In addition, the child and/or their family will be consulted to ensure that potential treatment items are highly functional and motivating to the greatest extent possible. Targeted areas will include accuracy of movement gestures in a range of syllable and word shapes, vowel accuracy, coarticulatory contexts including a range of consonant and vowel transitions, and varied stress patterns.

The generalization corpus will be used to examine carryover of treatment gains. This set of words/phrases consists of 45 words/phrases that will not be included in treatment for any participant. These words/phrases have been divided into 15 low complexity targets, 15 medium complexity targets, and 15 high complexity targets. Target complexity was determined according to word structure, segmental features, and lexical/phrasal stress. Word structure of targets follows a hierarchy of increasing complexity determined by syllable/word shape (e.g., CV, VC, CVC, CVCV, VCVC, CCVC, CVCVC, etc.), syllable number (e.g., monosyllabic, bisyllabic, multisyllabic words and phrases), and presence of adjacent consonants (e.g., CCVC; CVC CVC). Segmental complexity accounts for age of acquisition (i.e., Early 8, Mid 8, Late 8; [50]), consonant features (i.e., place, manner, voicing), and vowel characteristics (i.e., vowel height/advancement; monophthong, diphthong). Complexity of movement transitions considers whether targets contain the same or different consonant–vowel sequences (i.e., same consonants/vowels, varied consonants/same vowels, same consonant/varied vowels, varied consonants/varied vowels) and the extent of place/manner/voicing changes across phoneme sequences. Suprasegmental complexity is based on whether lexical and phrasal stress follows either a trochaic or iambic pattern. See Table 1 for details regarding each level of complexity. Children with severe CAS will produce the 30 low and medium complexity targets. Those with moderate CAS will produce the 30 medium and high complexity targets. The child’s complexity level will be determined from their initial speech assessments using a checklist that clinicians will complete. The 15 medium complexity non-treatment words will be elicited from all participants.

**Table 1 Tab1:** Target complexity framework

	**Word Structure**	**Segmental Complexity**	**Movement Sequences**	**Lexical Stress**
**Low Complexity**	CV VC CVC Reduplicated CVCV	**Consonants** Early consonants **Vowels** Simple vowels, diphtongs	Same consonant/vowel sequences	Trochaic
**Medium Complexity**	CVC CVCV VCVC	**Consonants** Early, mid, and some late consonants; Homorganic consonant clusters **Vowels** Simple vowels, diphthongs	Same and varied combinations of consonants (differing by place, manner, and/or voicing) and vowels	Mostly trochaic, some iambic
**High Complexity**	Multisyllabic words Phrases	**Consonants** Early, mid, and late consonants Homorganic & heterorganic consonant clusters **Vowels** Simple vowels, diphthongs	Varied combinations of consonants and vowels	Trochaic & iambic

#### Probe data

Treatment outcomes will be measured using probe data, which will be collected before, during, and following the intervention phase. The data collection schedule is presented in Table 2. Probe words consist of 50 items that include 20 individualized potential treatment targets and a 30-item generalization corpus. At each data collection session, one list of probe words will be presented in a randomized order with each word produced once. Probe data will be elicited in direct imitation (e.g., “Say, “apple") with no feedback or cues provided. The procedure for probe data collection is identical in baseline, treatment, and follow-up phases.

**Table 2 Tab2:** Data collection schedule

	**Low dose frequency**			**High dose frequency**		
**Study week**	***Treatment***	***Assessment***	***Assessment evaluates***	***Treatment***	***Assessment***	***Assessment evaluates***
-3 to -2		P1 (× 1), ICS, FOCUS 34	Baseline accuracy, intelligibility and participation		P1 (× 1), ICS, FOCUS 34	Baseline accuracy, intelligibility and participation
-1		P2 (× 3)			P2 (× 3)	
1	Tx1 Tx2	P3 (× 1)	Baseline accuracy (pre-Tx1)	Tx1 Tx2 Tx3 Tx4	P3 (× 1)	
2	Tx3 Tx4	-		Tx5 Tx6 Tx7 Tx8	P4 (× 1)	Accuracy after 6 Tx sessions (pre-Tx7)
3	Tx5 Tx6	-		Tx9 Tx10 Tx11 Tx12	-	
4	Tx7 Tx8	P4 (× 1)	Accuracy after 6 Tx sessions (pre-Tx7)	Tx13 Tx14 Tx15 Tx16	P5 (× 1)	Accuracy after 12 Tx sessions (pre-Tx13)
5	Tx9 Tx10	-		Tx17 Tx18 Tx19 Tx20	P6 (× 1)	Accuracy after 18 Tx sessions (pre-Tx19)
6	Tx11 Tx12	-		Tx21 Tx22 Tx23 Tx24	P7 (× 2), ICS, FOCUS 34	Accuracy after 24 Tx sessions (1-day post-Tx24), intelligibility and participation
7	Tx13 Tx14	P5 (× 1)	Accuracy after 12 Tx sessions (pre-Tx7)		P8 (× 3)	1-week post-Tx accuracy
8	Tx15 Tx16	-				
9	Tx17 Tx18	-				
10	Tx19 Tx20	P6 (× 1)	Accuracy after 18 Tx sessions (pre-Tx19)		P9 (× 2), ICS, FOCUS 34	4-week post-Tx accuracy, intelligibility and participation
11	Tx21 Tx22	-				
12	Tx23 Tx24	P7 (× 2), ICS, FOCUS 34	Accuracy after 24 Tx sessions (1-day post-Tx24), intelligibility and participation			
13		P8 (× 3)	1-week post-Tx accuracy			
16		P9(× 2), ICS, FOCUS 34	4-week post-Tx accuracy, intelligibility and participation			
18					P10 (× 3)	12-week post-Tx accuracy
24		P10 (× 3)	12-week post-Tx accuracy			

*P* Probe session, *ICS* Intelligibility in Context Scale [29], *FOCUS 34* Focus on Communication in Under Six [30], *Tx* Treatment

##### Baseline phase

Probe data will be collected five times during the baseline phase. Baseline probe data collection will be spread across three separate sessions over the two-to-three-week period prior to the start of treatment. One set of probe data will be collected during the first baseline session (P1), three sets will be collected at the second baseline session (P2) with a 15-min break between administrations, and one set will be gathered immediately prior to the first treatment session (P3).

##### Treatment phase

Probe data will be collected four times across the treatment phase. One set of probe data will be collected in the first 10 min of the 7^th^, 13^th^, and 19^th^ treatment sessions (P4, P5, P6, respectively). Two sets of probe data (with a 15-min break between administrations) will be collected on the day following the final treatment session (P7).

##### Follow-up phase

Probe data will be collected at 1 week, 4 weeks, and 12 weeks following the last treatment session to measure treatment gains, maintenance, and generalization of gains. Three sets of probe data will be collected at 1-week post (P8), two sets of probe data will be collected at 4-weeks post (P9), and three sets will be collected at 12-weeks post (P10). There will be a 15-min break between administrations of probe data. The follow-up schedule was selected to facilitate comparison with other CAS treatment studies [21, 22, 51].

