##### Additional assessments

Parents will complete the FOCUS-34 [30] and the ICS [29] one day following the last treatment session and four weeks post-treatment. The GFTA-3 [42] will be administered at one day post-treatment and four weeks post-treatment. Each of these sessions will take under 90 min, with breaks and game reinforcers given, as needed.

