Growth curve modeling considers change over time as an underlying latent process. In analyzing this process, a trajectory of change over time is established for each individual in a sample, and therefore, characteristics of the trajectory (e.g., slope) may vary across individuals and are treated as latent variables. These latent variables describe parameters of change and may be treated as independent, dependent, control, or mediating variables and be compared across groups. Specifically, the growth curve model will allow us to (a) compare the treatment effect between Low Dose Frequency treatment and High Dose Frequency treatment groups during the treatment stage; (b) compare groups on maintenance effects during the post-treatment stage; (c) explain variations in change by incorporating various predictors. The growth curve model will also allow us to model flexible patterns of change in time such as quadratic and piecewise forms. Analyses will be conducted using Mplus software 5.0 [33].

Throughout our modeling process, we will carefully consider potential confounders that should be added to the model as covariates, such as severity of impairment, number of blocks practiced per session, age, and sex of the children. In the presence of attrition, an intention to treat analysis will be performed and compared with the analysis done on the “per protocol” population whenever possible. Baseline characteristics of the completed and withdrawn participants will be compared to prevent selection bias in the conclusions. In addition, internal validity (i.e., how well the randomization worked to create similar study groups) will be checked by comparing the groups on relevant measures using analyses of variance.

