This study will compare two different treatment schedules and, consequently, it is imperative that children attend according to the prescribed schedule. While missing sessions due to illness such as COVID-19 cannot be avoided, it is possible to schedule study participation around other commitments such as vacations and holidays. To avoid preventable absences from treatment and follow-up sessions and ensure adherence to the study protocol, each clinician will work through the entirety of the study schedule with families prior to conducting baseline testing. Families will sign off in agreement to all dates from baseline through the 12-week follow-up before these activities begin.

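### A child who stops DTTC early has no reliably timed post-treatment outcome, because the probes are anchored to attended sessions or the end of treatment, yet an intention-to-treat analysis is promised

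*Protocol article*

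**What the plan says.** All of this is in the protocol article.

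- **During treatment** (Treatment phase): "One set of probe data will be collected in the first 10 min of the 7^th^, 13^th^, and 19^th^ treatment sessions". These are P4, P5 and P6.
- **End of treatment** (Treatment phase): two probe sets "will be collected on the day following the final treatment session (P7"). Table 2 describes the same probe as "Accuracy after 24 Tx sessions (1-day post-Tx24), intelligibility and participation".
- **Follow-up** (Follow-up phase): "Probe data will be collected at 1 week, 4 weeks, and 12 weeks following the last treatment session". These are P8, P9 and P10.
- **Parent measures** (Additional assessments): FOCUS-34 and ICS are completed "one day following the last treatment session and four weeks post-treatment".
- **Withdrawals** (Group allocation): when a participant withdraws before completing the study, the next child to enrol is put in the same arm as a substitute.
- **Analysis** (Statistical analysis plan): gains are computed from baseline to 1 day, 1 week, 4 weeks and 12 weeks post-treatment, and a growth-curve model is fitted to the repeated probes. On attrition: "In the presence of attrition, an intention to treat analysis will be performed and compared with the analysis done on the “per protocol” population whenever" this can be done.
- **Scheduling** (Potential limitations): "Families will sign off in agreement to all dates from baseline through the 12-week follow-up before these activities begin".

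**The concern.** For a child who attends all 24 sessions, the last session and session 24 are the same day and the schedule is clear. For a child who stops earlier they are different days, and the article does not say which one governs. It also does not separate stopping the sessions from leaving the study.

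An intention-to-treat analysis of the 1-day to 12-week gains needs those outcomes, taken at comparable times, on every randomised child. As written, an early stopper supplies either none of them or a set measured after a partial course but labelled as the others are.

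The article gives a reason to think stopping could differ by arm. Under Potential limitations it expects some families to see four visits a week as too great a burden, and it foresees frustration and fatigue in the children. One of its main predictions is better maintenance in the high-frequency arm at 4 and 12 weeks (Potential significance), which depends on the probes at risk. If children who are struggling leave the high-frequency arm and go unmeasured, the comparison moves towards that prediction. If the losses fall in the low-frequency arm, it moves the other way.

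**Working it through.** **1. The plan's own figure.** Targeted enrollment gives 60 children plus 6 for 10% attrition: 60 × 1.10 = 66, which reproduces. (Dividing instead, 60 / 0.90 = 66.7, rounds up to 67; the difference is immaterial here.) So about six early losses are foreseen, against 30 per group in the power statement.

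**2. The two anchors for one child.** Take a child who stops after session 10, with study weeks from Table 2.

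| | High frequency | Low frequency |
|---|---|---|
| Week of session 10 | 3 | 5 |
| Planned week of P7 | 6 | 12 |
| P7 timed from the child's own last session | about week 3 | about week 5 |
| P7 early by about | 6 − 3 = 3 weeks | 12 − 5 = 7 weeks |
| Planned week of P10 | 18 | 24 |
| P10 timed from the child's own last session | 3 + 12 = week 15 | 5 + 12 = week 17 |

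On the session-24 reading, P5 to P10 never occur for this child. On the last-session reading, P7 to P10 occur about 3 or 7 weeks early, depending on arm, and carry the label of a full-course outcome. On both readings the child has the baseline probes and P4.

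**3. What the planned analyses can recover.**
- The growth model can use baseline and any of P4–P6. For this child the only on-treatment point is P4, so on the session-24 reading the end-of-treatment and maintenance values are extrapolated.
- Comparing completers with withdrawals on baseline characteristics says nothing about how their outcomes differ.
- Coding a recurring reason for missingness as a covariate (Missing values) does not restore a missing outcome. If the reason were schedule burden, it could sit mostly in one arm and be entangled with the treatment effect.

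**4. Illustration of size.** Assumptions, none of them from the article: a completer-only contrast; six withdrawals; a deficit δ in the gain that withdrawn children would have shown, in SD units; and 0.35 read as SD units. Same-arm substitution fixes the denominators: each arm ends with 30 completers, so the number enrolled in an arm is 30 plus its withdrawals.

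Bias = (share withdrawn, high − share withdrawn, low) × δ

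- **All six in the high arm:** 6/36 − 0/30 = 0.167.
  - δ = 0.5: 0.083 SD, and 0.083 / 0.35 = 24%.
  - δ = 0.8: 0.133 SD, and 0.133 / 0.35 = 38%.
- **Five high, one low:** 5/35 − 1/31 = 0.143 − 0.032 = 0.111.
  - δ = 0.5: 0.055 SD, 16%.
  - δ = 0.8: 0.088 SD, 25%.
- **Three and three, same δ:** 3/33 − 3/33 = 0, so no bias.

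**The case against.** The case against has real weight.

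- **The text and Table 2 do not conflict for the course they describe.** Table 2 sets out 24 sessions, so its last session is session 24. They part only for a child whom neither addresses. A journal article may leave such children to the full protocol, and this one mentions a study manual that is not shown. This stands as far as it goes: the problem is an unsettled anchor, not an outright contradiction. But the article itself fixes the session-based timing, the substitution rule and the intention-to-treat promise, and those three do not fit together for an early stopper.
- **A reader might infer that early stoppers have no planned outcome at all.** The documents do not support that. Every child has baseline probes, a child who reaches session 7, 13 or 19 has P4, P5 or P6, and the Follow-up phase wording can be read as scheduling P8–P10 from the child's own last session.
- **A reader might infer that replaced children are dropped and that the intention-to-treat set is completers only.** Nothing says so. The article sets intention to treat against per protocol, which implies that non-completers belong to the former, and the growth model can use partial trajectories.
- **A reader might take stopping sessions to be withdrawal.** Group allocation speaks only of withdrawing before the study is complete. The article leaves the two undistinguished; it does not equate them.
- **Differential dropout is not established.** The burden remark concerns schedule preference and also says some families would prefer four visits a week. A $40 stipend per session is paid, and a 12-week course could lose families through its length. This stands, and it is why the figures are only illustrative.
- **Moving everyone to calendar dates would do harm.** A child making up sessions missed through illness could be given P7 before session 24, which would spoil the comparison at equal cumulative dose. This stands and limits the fix.

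**Conclusion.** The point holds for the post-treatment outcomes. Followed as written, the schedule gives a child who stops DTTC early either no P7–P10, ICS and FOCUS-34 results after baseline, or results taken weeks early under the same label. With same-arm substitution, the 1-day to 12-week gains would in practice rest largely on completers and substitutes. That is a consequence of the schedule, not something the article states, and the growth model softens it without removing it.

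The size is not known. In the assumed scenarios with unequal loss, the bias in a completer-only contrast is 0.06 to 0.13 SD, or 16% to 38% of 0.35; with equal loss and equal deficits it is zero. These figures depend on the assumed splits and deficits. They also depend on reading 0.35 in SD units, whereas the article scales it by the square root of the model variance. They do not estimate bias in the planned growth model.

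**What to change.** 1. State that stopping DTTC sessions is not withdrawal from the study.
2. Unless consent for data collection is withdrawn, collect P7–P10 for children who stop before session 24 on the dates the family has already signed: the planned session-24 date plus 1 day, 1 week, 4 weeks and 12 weeks. Collect ICS and FOCUS-34 at the 1-day and 4-week dates.
3. Keep the actual session-24 anchor for children who complete all 24 sessions, including those with made-up sessions.
4. Put the same wording in Treatment phase, Follow-up phase, Additional assessments and Table 2.
5. Keep every randomised child, including any who is replaced, in the assigned arm for the intention-to-treat analysis.

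The cost is protocol wording and a few visits that are already scheduled: at 10% attrition, about 6 children × 4 visits = 24 visits. Some families will decline, so some outcomes will still be missing.

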##### Additional assessments

Parents will complete the FOCUS-34 [30] and the ICS [29] one day following the last treatment session and four weeks post-treatment. The GFTA-3 [42] will be administered at one day post-treatment and four weeks post-treatment. Each of these sessions will take under 90 min, with breaks and game reinforcers given, as needed.

### Data management and storage

Eligibility and treatment data will be collected by community clinicians throughout the United States and Canada. All assessment and treatment sessions will be video recorded using an iPad 9 (64 GB, 10.2″ Display) and probe sessions will also be audio recorded. Once recordings are made, they will be transferred to SharePoint within 24 h to be processed, scored, transcribed, and stored by the research team.

### Statistical design

#### Outcome measures

The primary outcome measure is whole word accuracy which will be measured using the MACS scoring system [27]. The MACS was designed to specifically reflect areas of speech production most impacted in children with CAS through generating a composite score that reflects both segmental and suprasegmental accuracy at the whole-word level. The MACS rates production accuracy across the following categories: (1) segmental accuracy = accuracy of consonants and vowels; (2) word structure = maintenance of the targeted word shape; (3) prosody = accuracy of lexical stress in 2 + syllable words; (4) movement transitions = fluidity and smoothness of speech movements across sounds and syllables. Each of these categories is rated using a binary scale (0 = incorrect; 1 = correct). These ratings are then averaged to create the MACS composite score. The MACS score will be used to quantify production accuracy for all treatment targets and the generalization corpus produced within probe data collection. Whole word accuracy using the MACS will be measured across Baseline, Treatment, and Post-Treatment phases. Accuracy ratings will be compared between treated and untreated words to examine generalization effects [52].

Secondary outcome measures will include phoneme accuracy (Percent Phonemes Correct; [28]), speech intelligibility (ICS; [29]), and functional communication (FOCUS-34; [30]). Measures of speech intelligibility and functional communication will be completed by caregivers pre- and post-treatment.

### Statistical analysis plan

A Quasi-Poisson regression model will be used to calculate the effect size for the primary outcome measure of whole word accuracy (i.e., the MACS score). This model will be used to account for changes in the relationship between the mean and variance across various stages of treatment. A standard effect size assumes independence between the mean and variance. However, past work [55] has demonstrated that these values are not independent of one another across the experimental period (e.g., at post-treatment, higher accuracy often occurs in combination with more stable performance as compared to baseline where low accuracy occurs in combination with more variable productions). The quasi-Poisson model accounts for these changes in the relationship between the mean and variance to more accurately calculate effect sizes. Gains in whole-word accuracy will be calculated from Baseline to 1 day and 1 week post to capture treatment effects and from Baseline to 4 weeks post and 12 weeks post, respectively, to examine maintenance of treatment gains.

Given that multiple data points will be collected over time, data will also be analyzed using longitudinal growth curve modeling within the framework of Structural Equation Modeling [56, 57]. Growth curve modeling was chosen for its capacity of modeling within-participant change over time, as well as between-participant differences. It estimates the mean intercept and mean slope for the sample. Similar to the basic regression model, these effects are assumed fixed for all individuals in the sample. It also takes into account within-participant correlation among the repeated measurements by incorporating random components (i.e., individual variations around the mean intercept and around the mean slope).

Growth curve modeling considers change over time as an underlying latent process. In analyzing this process, a trajectory of change over time is established for each individual in a sample, and therefore, characteristics of the trajectory (e.g., slope) may vary across individuals and are treated as latent variables. These latent variables describe parameters of change and may be treated as independent, dependent, control, or mediating variables and be compared across groups. Specifically, the growth curve model will allow us to (a) compare the treatment effect between Low Dose Frequency treatment and High Dose Frequency treatment groups during the treatment stage; (b) compare groups on maintenance effects during the post-treatment stage; (c) explain variations in change by incorporating various predictors. The growth curve model will also allow us to model flexible patterns of change in time such as quadratic and piecewise forms. Analyses will be conducted using Mplus software 5.0 [33].

Throughout our modeling process, we will carefully consider potential confounders that should be added to the model as covariates, such as severity of impairment, number of blocks practiced per session, age, and sex of the children. In the presence of attrition, an intention to treat analysis will be performed and compared with the analysis done on the “per protocol” population whenever possible. Baseline characteristics of the completed and withdrawn participants will be compared to prevent selection bias in the conclusions. In addition, internal validity (i.e., how well the randomization worked to create similar study groups) will be checked by comparing the groups on relevant measures using analyses of variance.

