#### Group allocation

For participants who meet inclusionary criteria following the eligibility assessment, group allocation will be specified by the study statistician using a computer-generated random number list. The group assignments will be put into sequentially numbered, opaque, sealed envelopes with the specified group number indicated inside the envelope. This will help to conceal the randomization sequence until group assignments are made. The study statistician will generate confidential treatment assignments for participants 1 through 30 and participants will receive their group assignment in the order in which they are enrolled in the treatment phase. After 30 participants are enrolled, we will conduct preliminary group comparisons of participant demographics to determine the extent that the groups are balanced. If there are statistically significant differences between groups on potentially confounding demographic variables such as age, language ability, or speech severity, we will attempt to rebalance the groups for the subsequent 30 participants who are enrolled. Speech severity will be established through combined analysis of scores from dynamic motor speech skill assessment (DEMSS) and single word articulation testing (*GFTA-3*). In cases where a participant withdraws prior to the completion of the study, the next participant to enroll will be assigned to the same treatment condition to be the substitute. Participants and clinicians will be told which group each participant is assigned to by the research team after the informed consent document has been signed and eligibility has been determined by the eligibility assessments.

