### Data cleaning and preparation

Data will be securely stored and transferred in SharePoint folders. Trained research assistants will enter data into spreadsheets using participant identifiers. All data will be reviewed for valid values/data entry errors, outliers, and the extent and patterns of missing data. Consistency and logic checks that constitute standard review/cleaning procedures will be applied. The distributions of these measures across sessions will be summarized. Descriptive statistics will be used to describe measures at different periods in the study. Growth curve models allow us to quantify change from pre- to post-treatment and post-treatment to maintenance by interacting the treatment effect with time. Effect sizes for treatment will be compared between Low Dose Frequency treatment and High Dose Frequency treatment. The growth curve of each individual participant will be fit through random effect components, which control intra-participant correlation introduced by repeated measures. Covariates will also be included to control for any covariate imbalance between different treatment groups.

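### Whole word accuracy is compared as a gain from baseline with no stated adjustment for the five baseline MACS probes, and the covariates are left to be chosen during modelling or on observed imbalance

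*Protocol article*

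**What the plan says.** Under Outcome measures: "The primary outcome measure is whole word accuracy which will be measured using the MACS scoring system". Under Baseline phase: "Probe data will be collected five times during the baseline phase". These are one set at P1, three at P2 and one at P3.

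The Statistical analysis plan section describes two analyses of these data.

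- A quasi-Poisson regression gives the effect size: "Gains in whole-word accuracy will be calculated from Baseline to 1 day and 1 week post to capture treatment effects". Gains to 4 and 12 weeks are used for maintenance. No baseline MACS term is mentioned.
- In addition, "data will also be analyzed using longitudinal growth curve modeling within the framework of Structural Equation Modeling". This model has random components, described as "individual variations around the mean intercept and around the mean slope", and is the one said to compare the two schedules during treatment and afterwards. The power statement under Targeted enrollment also rests on a latent growth curve model.

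There are two statements on covariates. The Statistical analysis plan says "we will carefully consider potential confounders that should be added to the model as covariates", with severity, practice blocks per session, age and sex as examples. Data cleaning and preparation says "Covariates will also be included to control for any covariate imbalance between different treatment groups". Under Group allocation, severity is defined without reference to MACS: "Speech severity will be established through combined analysis of scores from dynamic motor speech skill assessment (DEMSS) and single word articulation testing".

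**The concern.** The child's own baseline MACS, on the same words, is likely to be the best single predictor of the later score, and the trial already pays to collect it five times. Subtracting it forces its coefficient to 1. If the true regression of the post-treatment score on baseline has a slope below 1, subtraction adds baseline noise to the comparison and over-corrects any chance difference between arms: the arm that happens to start higher then appears to gain less.

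A random-intercept, random-slope model does not by itself remove this. It does so if the two arms are given one baseline mean, or if the slope is conditioned on the intercept, and the article states neither. Severity is not a full substitute. It comes from other instruments and is only a candidate covariate, whereas MACS is scored on 20 individual targets and a corpus that varies with severity.

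With covariates still to be considered, and added for imbalance, the adjusted estimate depends on choices made after the arms can be compared. There are 30 children per arm, aged 2;6 to 7;11. The Discussion would read an undetected difference as support for choosing the schedule by resources and preference, so lost precision bears on that conclusion.

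**Working it through.** **The plan's own figure.** Targeted enrollment gives 30 per group, two-sided 5%, effect 0.35 and power 80%, from an Mplus simulation. The effect is scaled by the square root of a model variance that is not reported. Taking 0.35 as a plain standardised difference gives a noncentrality of 0.35 × √(30/2) = 1.356 and power of about Φ(1.356 − 1.960) = 27%. Reaching 80% would need 2 × (1.960 + 0.842)² / 0.35² ≈ 129 per arm. The stated 80% therefore depends on the unreported variances and can be neither reproduced nor refuted. A growth model with assumed variances (below) gives about 42% to 88%, so 80% is attainable.

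**Gain versus adjusted, using probe means.** Inputs from the article: p = 5 baseline sets; r = 2 post sets at 1 day (P7) or r = 3 at 1 week (P8). Assumed: equal variance (1) for every probe set, correlation w within a phase and b between baseline and post.

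- Variance of the post mean: A = [1 + (r − 1)w] / r
- Variance of the baseline mean: B = [1 + (p − 1)w] / p
- Gain: A + B − 2b
- Adjusted: A − b²/B

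Example with w = b = 0.5 and r = 2: A = 0.75 and B = 0.60. Gain = 0.35; adjusted = 0.75 − 0.25/0.60 = 0.333; ratio 0.95.

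To turn ratios into power, suppose the gain analysis has exactly 80% power. With 30 per arm that is a difference of 0.736 gain-score SDs. Adjustment divides the noncentrality 0.736 × √15 by the square root of the ratio, with 57 degrees of freedom.

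| r | w | b | Gain | Adjusted | Ratio | Power if gain has 80% |
|---|---|---|---|---|---|---|
| 3 | 0.3 | 0.3 | 0.373 | 0.329 | 0.88 | 85% |
| 2 | 0.5 | 0.5 | 0.350 | 0.333 | 0.95 | 82% |
| 2 | 0.7 | 0.7 | 0.210 | 0.205 | 0.98 | 81% |
| 3 | 0.9 | 0.9 | 0.053 | 0.053 | 0.99 | 80% |
| 2 | 0.8 | 0.7 | 0.340 | 0.317 | 0.93 | 83% |
| 2 | 0.8 | 0.5 | 0.740 | 0.602 | 0.81 | 87% |
| 3 | 0.9 | 0.3 | 1.253 | 0.836 | 0.67 | 93% |

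With one common correlation (w = b, first four rows) the range is about 80% to 85%. It reaches about 93% only when b is well below w. If the baseline SD is smaller than the post SD, the slope can approach 1 and the benefit vanishes.

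**Chance imbalance.** The slope of the post mean on the baseline mean is b/B. A baseline difference of one standard error, √(2B/30), shifts the gain contrast by (1 − b/B) × √(2B/30), in the direction against the arm that starts higher.

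- w = b = 0.5: (1 − 0.833) × 0.200 = 0.03 single-probe SD
- w = 0.8, b = 0.5: (1 − 0.595) × 0.237 = 0.10 single-probe SD

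**Growth curve model.** Assumed: intercept SD 1, residual SD 0.4, slope SD 0.3 to 0.7 over the treatment period, the ten probe sets from P1 to P7, 30 per arm. Variance of the arm-by-time effect with arm intercepts constrained equal, divided by that with intercepts free:

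- intercept–slope correlation 0: 0.99 to 1.00
- correlation −0.4: 0.84 to 0.88
- correlation −0.6: 0.66 to 0.76

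**The case against.** The strongest reply is that the gain calculation is not the whole analysis. The growth curve model uses all the probes, carries the arm comparison and underlies the power figure. The article says its latent variables may act as control variables, so conditioning on the intercept is open, and the parameterisation may sit in an analysis plan that is not shown. This stands. A reader might infer that whole word accuracy is analysed only as an unadjusted gain, or that the growth model fails to handle baseline. The text supports neither; it is silent on the intercepts. What remains is that the article does fix a gain for the primary outcome and does fix imbalance as a reason for adding covariates.

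The gain sentence also belongs to a quasi-Poisson model, so normal-theory change-score variances are only a guide to it. That stands too.

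On covariates, the list is illustrative and already includes severity, age and sex. A reader might infer that the analyses of variance decide which covariates enter. The article presents them as a check on the randomisation, not as a gate. Group allocation also plans a balance check after 30 children, with an attempt to rebalance the next 30. That may limit imbalance in age, language and severity, but it does not name MACS.

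Finally, a gain score is not biased over repeated randomisation. That is correct: the issue is precision and conditional error.

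**Conclusion.** The point holds as one of precision and pre-specification. The article expresses the primary outcome as a gain without naming baseline MACS as a covariate, leaves the growth model's treatment of baseline unstated, and does not close the covariate set before the arms are compared.

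The size is conditional on correlations that the article does not give. Relative to a gain analysis assumed to have 80% power, adjustment yields about 80% to 85% under one common correlation of 0.3 to 0.9. It yields up to about 93% where baseline predicts the post score weakly relative to within-phase repeatability. In the growth model the benefit is close to nil if intercept and slope are uncorrelated, and material only if they are negatively correlated. Adjustment has no material cost in any of these cases.

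Two stronger readings are not supported. A reader might infer that power would rise from 80% to about 90%. That follows from a single-baseline, single-post t-test on differences with correlation 0.5 (variance ratio (1 + 0.5)/2 = 0.75), and the plan specifies no such test. A reader might also infer the same loss for the ICS and FOCUS-34, but the article specifies no gain-score analysis for them.

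**What to change.** In the Statistical analysis plan section, state that every between-arm comparison of MACS (1 day, 1 week, 4 weeks, 12 weeks) adjusts for the mean of the P1 to P3 baseline probes on the same word set. This can be done by entering that mean as a covariate, or by fitting the growth curve model with the two arms' baseline means constrained equal, which randomisation justifies.

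Fix baseline severity (DEMSS and GFTA-3) and age as covariates regardless of observed balance. In Data cleaning and preparation, remove imbalance between arms as a reason for choosing covariates. Gains can still be reported descriptively.

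No new data are needed. The cost is about three degrees of freedom with 60 children, and the benefit will be small if the slope of the post-treatment score on baseline proves close to 1.
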